### Outcome Measures

The primary outcome of this study is a reduction in pain intensity in the lumbosacral region and legs (radiating pain) perceived by participants, assessed as the change in the 10 cm VAS score at day 30 and after 3 months from baseline.

The secondary outcomes of this study are improvement in functional disability due to LDH, assessed by the ODI, version 2.0; change in neurodynamic evaluation, assessed using the SLRT; improvement in QoL, assessed by the SF-36; comparison of dependence on allopathic analgesics; and assessment of safety and acceptability of the *marma* therapy in patients with LDH, assessed by the incidence of adverse events (AEs) associated with the therapy and compliance of patients to *marma* therapy.

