### Participant Timeline

Eligible participants, upon signing the informed consent form, are assessed for screening according to the criteria outlined in the study protocol. Spine examination and neurological assessment by a spine surgeon, systemic examination, SLRT, MRI of the lumbosacral spine, and laboratory investigations (including hemogram, liver function test, renal function test, C-reactive protein, hemoglobin A1c, random blood sugar, rheumatoid factor, and human leukocyte antigen B27 test) are done during the screening of participants before baseline evaluation. Patients undergoing any internal or external therapy or Ayurvedic medication for pain management are instructed to discontinue these treatments, and a baseline evaluation is conducted after a 1-week washout period.

At the baseline visit, general information for personal identification and demographic profiling is collected, medical history is recorded, and a clinical examination for general physical and systemic conditions is done, followed by a detailed neurological examination. Assessment of pain by the 10 cm VAS, functional disability by the ODI, and QoL using the SF-36 is done. The history of consumption of nonsteroidal anti-inflammatory drugs (NSAIDs) or analgesic medications during the last 14 days is also noted. The Ayurvedic parameters, such as *prakriti*, are also assessed at baseline.

The participants are assigned the treatment as per group allocation mentioned on the chit in the opaque sealed envelopes opened by the participant upon baseline evaluation. Each study participant is called daily for the assigned therapy (*marma* therapy or physiotherapy) for 4 weeks. Oral medication has continued for 12 weeks.

Follow-up and outcome assessments are conducted on days 7, 15, 21, 30, 45, 60, and 90. Any AE reported by a study participant is recorded at each visit and thoroughly assessed for causality. Ongoing events are managed through appropriate interventions, including referral to a higher center when necessary. A telephonic follow-up on day 75 is done to note any AEs, the need for rescue medication, and drug compliance. Details of assessments done during each visit of the study participant are given in Table 1.

**Table 1. T1:** Participant timeline.

Variable	Study period									
	Enrollment	Allocation	After allocation							
	Screening	Baseline	Day 7	Day 15	Day 21	Day 30	Day 45	Day 60	Day 75 (telephonic)	Day 90
Enrollment										
Information and written consent	✓									

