Eligibility evaluation	✓									
Allocation		✓								
Intervention										
Issue of oral medication to both groups		✓	✓	✓	✓	✓	✓	✓		
Administration of *Marma* therapy to group A and physiotherapy to group B		✓	✓	✓	✓	✓				
Outcome assessment										
Medical history and demographic profile		✓								
Clinical examination	✓	✓	✓	✓	✓	✓	✓	✓		✓
Participants’ categorization into acute, subacute, and chronic cases for both groups		✓								
Baseline characteristics		✓								
Pain assessment		✓	✓	✓	✓	✓	✓	✓	✓	✓
Functional disability and quality-of-life assessment		✓		✓		✓		✓		✓
Straight leg raise test and other maneuvers		✓		✓		✓		✓		✓
Laboratory and radiological investigations	✓									✓^a^
Ayurvedic parameter assessment	✓									✓
Drug or therapy compliance			✓	✓	✓	✓	✓	✓	✓	✓
Rescue medication			✓	✓	✓	✓	✓	✓	✓	✓
Adverse event recording			✓	✓	✓	✓	✓	✓	✓	✓

a Only magnetic resonance imaging was done.

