### Assignment of Interventions

The participants are randomized to 2 study groups in the ratio of 1:1. SPSS (version 15.0; IBM Corp) is used to generate the random number sequence. Allocation concealment is ensured by using the sequentially numbered, opaque, sealed envelope technique. The sequence of randomization and preparation of the sealed envelope technique is done centrally by the biostatistics unit at the sponsor’s headquarters. The envelopes are opened by the study participants after completion of the baseline assessment, and the intervention is given to them as per the group allocation. Both the participant and the investigator are aware of the group allocation at the end of the baseline assessment. This trial is an open-label study. However, the research personnel assessing the primary outcome and the secondary outcomes, namely, functional disability and neurodynamic evaluation, were not aware of the group to which participants were allocated.

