### Monitoring

A team of technical personnel from the sponsor organization monitors the progress of the trial through regular site visits and data monitoring. The project activities at the study site are supervised to ensure compliance with the standard operating procedures outlined in the protocol and Good Clinical Practice guidelines.

The AEs reported by the study participants on the telephone or during follow-up visits are recorded in a standard format, and adequate details are collected by the study team for investigating causality. Serious AEs will be reported to the IEC and the sponsor within the stipulated timelines.

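### The safety outcome is worded as therapy-associated adverse events for marma only; it should be all adverse events by randomised arm, which the trial already records

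*Protocol article*

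**What the plan says.** The last paragraph of the Introduction presents the trial as evaluating both efficacy and safety of marma therapy relative to standard physiotherapy.

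Outcome Measures lists safety last among the secondary outcomes, as "assessment of safety and acceptability of the *marma* therapy in patients with LDH", to be "assessed by the incidence of adverse events (AEs) associated with the therapy" together with compliance with marma therapy. Physiotherapy is not mentioned there. The analgesic outcome in the same sentence is worded as a "comparison of dependence on allopathic analgesics".

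On collection, Participant Timeline says: "Any AE reported by a study participant is recorded at each visit and thoroughly assessed for causality". The row "Adverse event recording" in Table 1 is ticked at every contact from day 7 to day 90, including the day 75 telephone call, and is not limited to one group. Monitoring adds that "adequate details are collected by the study team for investigating causality".

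On masking, Assignment of Interventions says: "Both the participant and the investigator are aware of the group allocation at the end of the baseline assessment". It then states that "the research personnel assessing the primary outcome and the secondary outcomes, namely, functional disability and neurodynamic evaluation, were not aware of the group". Adverse events and their causality are not on that list.

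**The concern.** The stated aim and the stated outcome do not match. The aim is comparative, while the outcome is an incidence for one therapy, apparently limited to events linked to it.

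Two things follow if the outcome is used as worded. First, a marma-only incidence has nothing beside it, so a reader cannot tell whether it is higher or lower than under physiotherapy. Second, if the count is limited to attributed events, it varies with how readily events are attributed. Both arms take trayodashanga guggulu for 12 weeks and may use rescue analgesics, so an event in the marma arm has other candidate causes. The judgement between them is not described as masked.

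Safety is named in the Objective. Adverse event reports also carry much of the safety assessment, because the footnote to Table 1 says that only MRI was done among the day 90 investigations.

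**Working it through.** The article gives no adverse event rate or safety calculation, so there is no figure to reproduce. The check is mainly a comparison of its statements.

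**1. Aim against outcome.** The Introduction compares safety with physiotherapy. Outcome Measures measures safety of marma only. The analgesic outcome beside it is explicitly a comparison, so the two are worded differently within one sentence.

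**2. Attribution against masking.** Every reported event is assessed for causality (Participant Timeline), and the study team collects the details for this (Monitoring). The investigator knows the allocation. Masked assessment covers the primary outcome, functional disability and neurodynamic evaluation. Causality is therefore outside the stated masking. Who makes the judgement is not stated.

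**3. What is recorded.** Any reported event is recorded, whatever its cause, at every post-baseline contact and with no limit to one arm. The all-cause data by randomised arm will exist.

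**4. How far the worded outcome depends on attribution (assumed values).** Let r be the proportion of marma participants with any event, and a the probability that such a participant has an event attributed to the therapy. The reported incidence is r × a.

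| r (assumed) | a = 0.4 | a = 0.8 |
|---|---|---|
| 10% | 4% | 8% |
| 20% | 8% | 16% |
| 30% | 12% | 24% |

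For any r, moving a from 0.4 to 0.8 doubles the reported incidence with no change in what participants experienced. An all-cause count does not contain a.

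**5. What the all-cause comparison can deliver.** Inputs: 45 per arm (Sample Size); event rates assumed.

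- The 95% CI half-width is 1.96 × √[p1(1−p1)/45 + p2(1−p2)/45].
- For 10% v 20%: 1.96 × √(0.0020 + 0.0036) = 1.96 × 0.0745 = 14.6 percentage points.
- For 20% v 20%: 1.96 × √(2 × 0.16/45) = 1.96 × 0.0843 = 16.5 percentage points.
- Power at two-sided 5% (normal approximation, pooled variance under the null) is about 26% for 10% v 20% and about 82% for 10% v 35%.

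Only large differences would be detected, so the interval is more useful than a test.

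**The case against.** The strongest reply is that this is one phrase in a condensed article. All events are recorded in both arms. Serious events go to the ethics committee and sponsor with no condition of relatedness. Data Analysis plans frequencies, percentages and between-group comparisons in general terms, and the abstract commits to standard reporting guidelines. An all-event table by arm may well be in the full protocol or analysis plan. The phrase might also mean events occurring during the therapy rather than events judged to be caused by it.

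Much of this stands, and it rules out several stronger readings that a reader might infer:

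- *That the trial cannot give a randomised safety comparison.* The data allow one and nothing excludes it. The limitation lies in the outcome as worded.
- *That causality is judged by staff who know the arm.* This is plausible, but the article names no assessor. It supports only that causality is not among the masked assessments.
- *That events judged unrelated are discarded, or that the outcome favours marma.* The article says neither. The direction of any attribution error is unknown, and it could equally inflate the marma count.
- *That an all-cause comparison would be unbiased.* It removes the dependence on attribution. Events are still self-reported by participants who know their treatment.

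The reply does not remove the mismatch between aim and outcome, since the article itself states both. If the phrase means events during therapy, the attribution concern falls away, but the outcome still covers one arm only.

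**Conclusion.** The point holds in a limited form. The safety outcome as worded covers marma only and, on a causal reading, depends on attribution that may be unmasked. It therefore does not supply the comparison with physiotherapy that the Introduction describes. This is a stated definition that can be improved, not a missing detail, and it does not touch the primary outcome.

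Its numerical effect cannot be derived from the article. The doubling shown above rests on assumed attribution probabilities of 0.4 and 0.8 and shows only sensitivity, not likely error. The causal reading is itself an inference, supported by the article's statement that events are assessed for causality.

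**What to change.** Define the safety outcome as the number and proportion of participants with any adverse event, and with any serious adverse event, from baseline to day 90 by randomised arm, regardless of causality. Give the between-arm difference with a 95% CI. Keep therapy-attributed events as a supportive listing, and state who judged causality and whether they knew the allocation.

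The Results section says that data cleaning is complete and analysis still to be finished. The change should therefore be documented before results by arm are seen, through the route in Protocol Amendments (report to the sponsor and ethics committee with reasons). If results by arm have already been seen, label it post hoc.

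The cost is one reworded outcome and one table, with no new data. There are three downsides: the reported incidence will look higher than an attributed count, the comparison will be imprecise with 45 per arm, and reporting bias from unmasked participants will remain. The Results section reports 70 of 90 participants (77.8%) with completed final follow-up, so the table should also show how many in each arm were followed to day 90.

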### Participant Timeline

Eligible participants, upon signing the informed consent form, are assessed for screening according to the criteria outlined in the study protocol. Spine examination and neurological assessment by a spine surgeon, systemic examination, SLRT, MRI of the lumbosacral spine, and laboratory investigations (including hemogram, liver function test, renal function test, C-reactive protein, hemoglobin A1c, random blood sugar, rheumatoid factor, and human leukocyte antigen B27 test) are done during the screening of participants before baseline evaluation. Patients undergoing any internal or external therapy or Ayurvedic medication for pain management are instructed to discontinue these treatments, and a baseline evaluation is conducted after a 1-week washout period.

At the baseline visit, general information for personal identification and demographic profiling is collected, medical history is recorded, and a clinical examination for general physical and systemic conditions is done, followed by a detailed neurological examination. Assessment of pain by the 10 cm VAS, functional disability by the ODI, and QoL using the SF-36 is done. The history of consumption of nonsteroidal anti-inflammatory drugs (NSAIDs) or analgesic medications during the last 14 days is also noted. The Ayurvedic parameters, such as *prakriti*, are also assessed at baseline.

The participants are assigned the treatment as per group allocation mentioned on the chit in the opaque sealed envelopes opened by the participant upon baseline evaluation. Each study participant is called daily for the assigned therapy (*marma* therapy or physiotherapy) for 4 weeks. Oral medication has continued for 12 weeks.

Follow-up and outcome assessments are conducted on days 7, 15, 21, 30, 45, 60, and 90. Any AE reported by a study participant is recorded at each visit and thoroughly assessed for causality. Ongoing events are managed through appropriate interventions, including referral to a higher center when necessary. A telephonic follow-up on day 75 is done to note any AEs, the need for rescue medication, and drug compliance. Details of assessments done during each visit of the study participant are given in Table 1.

**Table 1. T1:** Participant timeline.

Variable	Study period									
	Enrollment	Allocation	After allocation							
	Screening	Baseline	Day 7	Day 15	Day 21	Day 30	Day 45	Day 60	Day 75 (telephonic)	Day 90
Enrollment										
Information and written consent	✓									
Eligibility evaluation	✓									
Allocation		✓								
Intervention										
Issue of oral medication to both groups		✓	✓	✓	✓	✓	✓	✓		
Administration of *Marma* therapy to group A and physiotherapy to group B		✓	✓	✓	✓	✓				
Outcome assessment										
Medical history and demographic profile		✓								
Clinical examination	✓	✓	✓	✓	✓	✓	✓	✓		✓
Participants’ categorization into acute, subacute, and chronic cases for both groups		✓								
Baseline characteristics		✓								
Pain assessment		✓	✓	✓	✓	✓	✓	✓	✓	✓
Functional disability and quality-of-life assessment		✓		✓		✓		✓		✓
Straight leg raise test and other maneuvers		✓		✓		✓		✓		✓
Laboratory and radiological investigations	✓									✓^a^
Ayurvedic parameter assessment	✓									✓
Drug or therapy compliance			✓	✓	✓	✓	✓	✓	✓	✓
Rescue medication			✓	✓	✓	✓	✓	✓	✓	✓
Adverse event recording			✓	✓	✓	✓	✓	✓	✓	✓

a Only magnetic resonance imaging was done.

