### Eligibility Criteria

#### Inclusion Criteria

Participants of any sex, aged 30-60 years, diagnosed with lumbar radiculopathy with unilateral radiating pain (either left or right lower limb) due to intervertebral disc herniation confirmed by magnetic resonance imaging (MRI; disc herniation between L3 and S1 levels at a single or double level) and without any evident neurological deficit are included. Participants having a positive straight leg raise test (SLRT; ipsilateral or contralateral pain in the leg, buttock, or back at ≤70° of leg elevation, with pain typically worsened by dorsiflexion of the ankle or neck flexion after slowly lowering the leg until the patient no longer feels pain) and those who are willing to adhere to the study protocol for a period of 3 months are included in this study.

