### Sample Size

A previous study that included physiotherapy as an intervention reported a mean VAS score for back pain of 3.05 (SD 1.36) points after treatment [11]. This was considered to anticipate an improvement of at least 2.79 points after *marma* therapy. Assuming a between-group difference of 1 point, with 80% power at 5% level of significance, the derived sample size was 72 participants. Furthermore, assuming a 20% attrition rate, the final sample size for this study was 90 participants, randomly allocated to the 2 groups in a 1:1 ratio (n=45, 50% participants per group). The effect size will be determined after the data analysis is completed.

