### Data Analysis

After verification for accuracy, all collected data will be anonymized prior to statistical analysis. All analyses will follow both the intention-to-treat and per-protocol principles to evaluate the robustness and sensitivity of the results. Any missing or incomplete responses will be addressed through Bayesian imputation. To make the imputation robust, regression-based imputation will also be applied if sufficient information is available in the data. Furthermore, the data will be used for descriptive analysis. Categorical variables will be described as frequencies and percentages, while continuous variables will be summarized as mean (SD) or median (IQR), depending on the distribution of the data (normal or skewed). Inferential analyses will be performed after descriptive analysis of the data. For within-group comparisons, data will be analyzed using the paired 2-tailed t test or the Wilcoxon signed-rank test, depending on the distribution of the data for pre-post observations. Between-group comparisons will be performed using the independent-samples *t* test or Mann-Whitney *U* test, depending on the normality of the data.

Repeated-measures ANOVA or the Friedman test will be used for within-group and between-group analyses of the outcomes assessed at multiple time points. The generalized estimating equation and the repeated-measures ANOVA, along with factor analysis, will also be performed if any confounding factors are found during the analysis. Analysis of covariance will be performed if baseline differences between groups are observed. A 2-sided significance level of 5% will be considered for all analyses. All statistical analyses will be performed using Stata software (version 16.1; StataCorp).

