*Marma* points are defined as vital anatomical sites where 2 or more bodily structures—such as muscles, veins, ligaments, bones, or joints—intersect. Etymologically, the Sanskrit term “*marma”* translates to “hidden” or “secret.” The *Sushruta* Samhita classically enumerates 107 such points. The corresponding therapeutic modality, *marma chikitsa,* involves applying targeted pressure to these junctions. This intervention is postulated to facilitate the movement of *prana* (vital energy) through a sophisticated network of subtle channels (*nadis*)*,* ultimately producing symptomatic relief, including analgesia [7]. *Marma chikitsa* is primarily practiced in southern India by traditional medicine healers and schools of martial arts, especially for various acute or chronic musculoskeletal and neuromuscular conditions. However, some practitioners also treat many systemic diseases using *marma chikitsa*, also popularly known as *varmam* in the Tamil language.

If *marma* therapy is demonstrated to be effective and safe in managing pain and enhancing QoL by reducing disability associated with LDH, it may be further evaluated in larger studies to strengthen the evidence base for its effectiveness. Additionally, training a greater number of traditional medicine practitioners in this approach could enable its integration into OPD-level care for patients with LDH. Such simple, noninvasive interventions have the potential to decrease dependence on oral analgesics, such as NSAIDs, among individuals with chronic pain.

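### Acute, subacute or chronic class is recorded at baseline but can enter the VAS comparison only through a data-triggered adjustment, at a cost in precision and analyst discretion

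*Protocol article*

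**What the plan says.** - **Eligibility.** Inclusion Criteria admits patients "diagnosed with lumbar radiculopathy with unilateral radiating pain (either left or right lower limb) due to intervertebral disc herniation confirmed by magnetic resonance imaging". Neither the inclusion nor the exclusion criteria limit how long symptoms have lasted.
- **Baseline classification.** Table 1 under Participant Timeline schedules "categorization into acute, subacute, and chronic cases for both groups" at the baseline visit.
- **Randomisation.** Assignment of Interventions states: "The participants are randomized to 2 study groups in the ratio of 1:1". It describes a computer-generated sequence in sealed envelopes and names no stratification factor.
- **Main comparison.** Data Analysis states: "Between-group comparisons will be performed using the independent-samples" t test, or the Mann-Whitney test if the data are not normal. Neither adjusts for anything.
- **Adjustment rule.** The same section adds: "Analysis of covariance will be performed if baseline differences between groups are observed". Generalised estimating equations and repeated-measures ANOVA "will also be performed if any confounding factors are found during the analysis". No covariate is named, and the article does not say how a difference or a confounder is to be recognised.

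**The concern.** Recent-onset and long-standing radiculopathy may run different courses over 30 to 90 days whichever therapy is given. If so, the duration class explains part of the spread in VAS change, and a comparison that ignores it is less precise than it could be. The protocol treats the class as worth recording in every participant, yet the only stated route into the analysis is a rule triggered by the observed data.

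That rule has two weaknesses. It uses the covariate only when the arms happen to look different, although the gain in precision from a prognostic covariate does not depend on imbalance. It also leaves the analyst to decide, with allocation known in an open-label trial, whether to adjust and for what. Precision is worth protecting: Results reports 70 of 90 participants with a completed final follow-up, against 72 planned as evaluable.

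**Working it through.** **Inputs from the article.** Sample Size gives a "mean VAS score for back pain of 3.05 (SD 1.36) points after treatment", a target difference of 1 point, 80% power, 5% significance, 72 participants, and 90 after 20% attrition. Data Analysis makes the test two-sided.

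**The plan's own figure.** n per arm = 2(1.96 + 0.84)² × 1.36² / 1² = 29.03, so 30 per arm and 60 in total (62 by the t distribution). The stated inputs do not give 72. The attrition step does reproduce: 72 / 0.80 = 90. This mismatch is a separate matter; 36 per arm is used below because it is the planned evaluable number.

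**Assumptions, because the article gives no figures.** Two classes for simplicity; share of one class p = 0.3 to 0.5; gap D in mean VAS change between classes = 1 to 2 points, the same in both arms; true arm difference 1 point.

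**Reference power.** SE = 1.36 × √(2/36) = 0.321. Power = Φ(1/0.321 − 1.96) = 0.88.

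**Case A: 1.36 is the within-class SD.** Unadjusted SD = √(1.36² + p(1−p)D²).

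| D | Unadjusted SD (p = 0.3; 0.5) | Unadjusted power | Adjusted power |
|---|---|---|---|
| 1 | 1.435; 1.449 | 0.84; 0.83 | 0.88 |
| 1.5 | 1.524; 1.553 | 0.80; 0.78 | 0.88 |
| 2 | 1.640; 1.688 | 0.74; 0.71 | 0.88 |

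With all 45 per arm analysed, unadjusted power is 0.91 (D = 1) or 0.80-0.82 (D = 2), against 0.94 adjusted.

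**Case B: 1.36 already contains the class spread.** Unadjusted power stays at 0.88. Within-class SD = √(1.36² − p(1−p)D²), which is 1.280 or 1.265 at D = 1. Adjusted power is then 0.91-0.92.

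**Does ignoring the class bias the test?** Under a true null with 36 per arm and p = 0.5, the simulated type I error of the unadjusted t test was 0.048 with no class gap and 0.052 with a 2-point gap (10,000 runs each). Chance imbalance is also not a second harm on top of the larger SD. The variance of the arm difference is 2 × 1.36²/n + D² × 2p(1−p)/n, and its second term is exactly D² times the variance of the imbalance in class share.

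**How well would the trigger work?** With 45 per arm, the SD of the imbalance is √(2p(1−p)/45) = 0.097 to 0.105. A 15-percentage-point imbalance gives z = 1.55 to 1.42, two-sided p about 0.12 to 0.15. A check by significance test, if that is what is meant, would not flag it. Yet it moves the estimate in that sample by 0.15 × 1 = 0.15 points or 0.15 × 2 = 0.30 points.

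**What can class-specific results show?** With three equal classes and 36 per arm, each class has about 12 per arm. The 95% half-width is 2.07 × 1.36 × √(2/12) = 1.15 points, wider than the 1-point target.

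**The case against.** The article is a condensed protocol, and covariate lists and subgroup tables are commonly left to an analysis plan that is not shown. Broad eligibility and unstratified randomisation are legitimate choices. The conditional ANCOVA and the confounder clause could take up the class if the arms differed markedly. The power loss rests on assumed shares and gaps and on reading 1.36 as purely within-class; at a 1-point gap, power stays above the planned 80% even then.

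Most of this stands. The absence of a subgroup table or covariate list is no finding, and the effect may be small. What remains is that Data Analysis does state an adjustment rule, and that rule makes the use of a prognostic covariate depend on the observed data.

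A reader might infer three stronger points that the article does not support:

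- **That a chance excess of acute cases biases the result.** It is sampling error, which the standard error already covers, and the 5% level holds. The simulation applies to the unadjusted test used throughout; it does not cover a choice between analyses made after seeing results.
- **That without an untreated arm the therapies cannot be separated from natural recovery.** Randomisation equalises the class mix in expectation, so the contrast between two active arms is not affected.
- **That the article draws an unsupported conclusion about chronic pain.** The Discussion says only that simple noninvasive interventions have potential to "decrease dependence on oral analgesics, such as NSAIDs, among individuals with chronic pain", after a condition that efficacy be shown. The abstract's conclusion is also conditional and concerns patients with disc herniation.

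**Conclusion.** The point holds as one of precision and analyst discretion, not of validity. On the assumptions above, leaving the class out costs about 4 percentage points of power at a 1-point gap and about 14 to 17 at a 2-point gap if 1.36 is within-class; power falls below 80% only from a gap of about 1.5 points. If 1.36 already includes the class spread, nothing is lost against the plan, but adjustment would still gain about 3 to 4 percentage points at a 1-point gap. The article does not say which reading of 1.36 applies. The adjusted figures ignore the few degrees of freedom that the extra terms use.

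No analysis named in the article would show an effect in chronic cases, so the result should not be extended to chronic pain in particular unless that class's estimate is shown, with its limited precision made plain.

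**What to change.** Replace the conditional ANCOVA rule with a fixed model for VAS at day 30 and day 90 containing arm, baseline VAS and baseline duration class, whatever imbalance is observed. Use the class as recorded at baseline and state its cut-offs with the results. Commit and date the rule before between-arm results are seen. The article says analysis is under way, so if any such results are already known, say so and label the adjusted model accordingly.

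Report the arm difference within each class with its 95% CI as descriptive only. Make no statement specific to chronic pain without the chronic-class estimate beside it.

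The cost is small: no new data, one term for baseline VAS, two for a three-level class, one table, and notice of the changed method to the sponsor and ethics committee as Protocol Amendments requires. Stratified randomisation by class is possible only in a follow-on trial, because all 90 participants are enrolled.
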